**Table 2 Tab2:** **Programme of guidance for participants from peer mentors**

*Session 1: Orientation, motivation and preparation*	Aim: introduce intervention and increase perceived value of making changes.
	Elicit participant view and increase motivation by reinforcing change talk. Instruction on use of Ieso Digital Health platform, vodcasts, APT strategies (that is, reflection tasks, implementation intentions, behavioural experiments). Review individual priorities to determine the order for proceeding through the four core workbook chapters.
*Session 2: Cognitive strengths and challenges*	Aim: increase flexibility, spontaneity and bigger picture thinking by following APT structure.
*Session 3: Social strengths and challenges*	Aim: support making changes in social context and identifying family relationships and healing ruptures.
	Follow APT process to enlist social support through friends, family, and work colleagues.
*Session 4: Nutrition*	Aim: review strategies for reducing avoidance behaviours (such as restriction, vomiting, or exercise).
	Follow APT with planning and anticipating obstacles, such as stress or abdominal discomfort.
*Session 5: Emotional strengths and challenges*	Aim: review strategies for increased emotional expression toward others (for example, through writing, openness), reducing maladaptive emotional regulation, enhancing self-compassion and nurturance.
*Session 6: Consolidation and re-setting goals*	Aim: exchange of ‘goodbye letters’.
	Offer a summary of progress and suggestions for further goals. Develop a set of personal resources (for example, vodcasts, written materials) to maintain change over time.

APT, ‘awareness, planning, try it’.

The workbook is organized into six sections: introduction to the intervention; separate modules detailing cognitive, emotional, social or interpersonal, and nutritional factors; and a summary section for future planning and integration of content. Each section follows a similar format and includes ‘*awareness*, *planning* and *try it*’ (APT) sections. *Awareness* includes psychoeducation and reflective exercises. *Precise planning* includes implementation of intention strategies for specific, foreseeable obstacles, in order to keep the overall goal of change in mind (in the form of ‘if… then’ statements) and using daily living prompts as hooks for new habits. *Try it* exercises include small behavioural experiments that encourage patients to take small, manageable risks in challenging thoughts, behaviours, and patterns related to eating disorders as they work toward recovery. The workbook is therefore customizable to meet individual needs; the chapters are allocated one to a week but may be utilized in whichever order participants see fit (except for the introductory and concluding chapters), based on level of confidence and sense of priority. The introduction section includes exercises focused on evaluating and increasing readiness to recover and identifying priorities and reasons for change, followed by APT goals setting. The summary section includes exercises for reflecting on the skills learned in the previous sections, the progress that has been made and re-evaluating the reasons for and one’s confidence to change. Each of the cognitive, emotional, social and nutritional modules target the difficulties a patient might experience in the respective area through various engaging exercises (for example, *cognitive module*: practising comprehensive, flexible thinking; *emotional module*: attending to positive emotions and building self-compassion; *social and interpersonal module*: strengthening relationships; *nutritional module*: confronting avoidance and managing cravings and purgative impulses; see Table 2).

A total of 60 vodcasts are downloadable from a secure website (Ieso Digital Health; http://www.iesohealth.com/) and participants are encouraged to save these locally on internet-capable mobile devices, such as iPods, iPhones, or Android phones. Consistent with the organization of the accompanying workbook, vodcasts are organized into six categories (that is, one set of vodcasts for each workbook section), and each vodcast lasts approximately 90 to 180 seconds. The ‘recovery narrative’ vodcasts were recorded via semistructured interviews conducted with recovered patients as they described what was helpful for their recovery, what they wished they had known at the time of their illness, and their descriptions of the nature of their recovery experiences. Nondistracting, soothing animations were added to complement the recovery narratives. Finally, each vodcast ends with a brief, written prompt that is directly linked to the content of that vodcast as a way to promote additional reflection, planning and active behaviour change.

In addition to the recovery narratives, the vodcast directory includes ‘skills-sharing’ vodcasts that are focused on helping patients gain specific skills for changing eating disorder behaviours (for example, managing food cravings, mindful eating, managing distressing emotions, focusing on the bigger picture and flexible thinking, and building self-compassion). Participants are also advised to download their own relaxation, mindfulness, and distraction podcasts in addition to those provided within the collection of vodcasts.

In total, 10 to 15 peer mentors will be trained, to allow for attrition. The purpose of the guidance is not to provide an additional stand-alone intervention, but rather, to offer support to patients in using the self-help materials effectively and purposefully. Peer mentors are individuals with past experience of eating disorders who have sufficient time for training, supervision and coaching and are trained in professions allied to medicine or equivalent (psychology, counselling) or teaching. Individuals with clinically significant levels of baseline anxiety, depression or eating disorder symptoms are excluded. Comprehensive training for task-sharing interventions involves three important components: participation in an introductory workshop delivered by an expert, reading or review of workbooks or other written materials that detail the intervention, and administration of the intervention under close supervision of treatment experts [2]. Peer mentors will receive all of these training components prior to delivering the *Recovery* MANTRA intervention.

The curriculum currently used for training and supervision of carer coaches will be adapted for training peer mentors. In particular, the peer mentors will receive three days of training in motivational interviewing, during which they will also become familiarized with the *Recovery* MANTRA materials and practise using the online text-chat delivery system. For the duration of their involvement in the project, the peer mentors will also receive weekly clinical supervision and will undergo regular assessment of their eating disorder symptoms and mood. Copies of the text-chat messages between the peer mentor and the participant will be used for supervision and to assess treatment quality and fidelity.

### Fidelity and adherence to model

Peer mentors will be assigned study participants only after they have demonstrated sufficient competence with training samples (that is, the training samples will have details of patients who will not be used within the study). Adherence and fidelity to the motivational interviewing model will be monitored by an analysis of a random selection of transcripts (sessions 2 to 5) using the Motivational Interviewing Treatment Integrity rating system, a validated and reliable behavioural coding system used to measure treatment integrity in motivational interviewing [38]. A simplified version of the Revised Cognitive Therapy Scale [39] will be adapted specifically for this intervention to address the more goal-driven aspects of the programme.

### Peer mentor assessments

Peer mentors will complete a demographic questionnaire upon enrolment and the EDE-QS and DASS-21 at baseline and every 3 months for the duration of their involvement in the project.

### Treatment as usual assessment

Treatment as usual will vary between centres and this will impact the effect size of the intervention [50]. We will therefore conduct structured interviews with clinicians at each study site to clarify the nature of treatment as usual at each centre. We will also use an adapted form of the Client Service Receipt Inventory (a well-established tool used in health economics) to track the amount of treatment received over the year. The inventory will be administered at 6-week and 6-month, to measure patients’ service usage.

### Outcome assessment

The primary outcome variable is patient BMI at the end of the 6-week intervention (treatment as usual versus *Recovery* MANTRA). The secondary outcome variables are patient BMI at 6-month and follow-up and eating disorder symptoms (assessed by EDE-Q scores) at 6-week and 6-month follow-up (treatment as usual versus *Recovery* MANTRA). The hypothesized mediators and moderators of primary and secondary outcomes include mood (DASS-21), perceived work or social adjustment (Work and Social Adjustment Scale), motivation and confidence to change (visual analogue scale and ACMTQ), cognitive flexibility, and perceived alliance with therapist and peer mentor. Moreover, the trajectories of change in eating disorder symptoms (weekly EDE-QS), perceived alliance with peer mentors (assessed weekly), and mood, confidence or motivation, connection to others, hope and adherence or satisfaction with treatment plan (assessed daily via ultra-brief surveys) will predict the primary and secondary outcomes. Exploratory outcomes include the impact of guidance delivery on peer mentors’ eating disorder symptoms and mood (assessed via a feedback form) and treatment adherence or fidelity and acceptability (assessed via a feedback form) on secondary outcomes.

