#### Tertiary

Do the domains identified by the underlying cognitive-interpersonal theoretical model (including motivation, hope, and confidence to change, anxiety, stress, and depression, perceived therapeutic alliance, work and social adjustment, social support, and increased cognitive flexibility) moderate or mediate changes in primary and secondary outcomes? Does the trajectory of daily process measures and weekly eating disorder symptoms measures predict outcomes (BMI and eating disorder symptoms) at 6-month follow-up?

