**Table 1 Tab1:** **Schedule of assessments in**
***Recovery***
**MANTRA**

**Assessment**	**Eligibility screening**	**Baseline**	**Daily, for 6 weeks**	**Weekly, for 6 weeks**	**End of 6 weeks**	**6-month follow-up**
Participant’s information, informed consent, screening	X					
Clinical and demographic information		X				
Body mass index		X		X	X	X
Eating Disorder Examination Questionnaire		X			X	X
Depression Anxiety Stress Scale		X			X	X
Work and Social Adjustment Scale		X			X	X
The Autonomous and Controlled Motivations for Treatment Questionnaire		X			X	
Eating Disorder Examination Questionnaire - Short				X		
Daily assessments			X			
Client Service Receipt Inventory						X
Visual analogue scale: confidence and motivation to change		X			X	
Cognitive flexibility		X			X	
Patient alliance with therapist		X			X	
Patient alliance with peer mentor				X		

Daily assessments employ visual analogue scales and follow the day reconstruction method to measure daily mood, motivation, confidence, treatment adherence and connectedness.

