## Expected results

### Quantitative data analysis

This exploratory hypothesis testing study is designed to assess our theorized model of maintenance and change in anorexia nervosa (Figure 1). The time trend in weight and symptoms of anorexia nervosa over 6 months for each person will be estimated using mixed-effects regression models with structured covariance patterns to account for autocorrelation of repeated measures [51,52]. Models will test for linear and curvilinear change over time. The difference between the groups in the rate of change over time will then be examined using group-by-time interaction. Variation within individuals will be modelled as ‘Level 1’ and will include daily survey data, and variation between individuals (including the intercept and slope) will be modelled as ‘Level 2’. All continuous variables will be grand mean centred and results will be modelled using random intercept and slopes. Separate analyses will regress (1) participants’ weight change (baseline to 6-month follow-up) on mood, (2) participants’ weight change (baseline to 6-month follow-up) on motivation to change and on confidence to change and (3) treatment condition on repeated assessment of weight.

Moderator and mediator analyses will be performed using the regression-based bootstrapping approach described by Hayes [53]. Bias corrected bootstrap confidence intervals will be used to test moderators and mediators based upon 10,000 bootstrap samples. Analyses will be conducted using the PROCESS macro [54].

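### Mediation of week-6 BMI and EDE-Q by the named questionnaires has no time order, because in Table 1 mediator and outcome share the same assessment point

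*Protocol article*

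**What the plan says.** Under Outcome assessment the protocol article fixes the endpoint: "The primary outcome variable is patient BMI at the end of the 6-week intervention". EDE-Q at 6 weeks and at 6 months, and BMI at 6 months, are secondary. The same section then says: "The hypothesized mediators and moderators of primary and secondary outcomes include mood (DASS-21), perceived work or social adjustment". The list continues with the visual analogue scales and ACMTQ for motivation and confidence, cognitive flexibility, and alliance with therapist and with peer mentor. That makes seven measures.

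The tertiary research question asks whether the model's domains "moderate or mediate changes in primary and secondary outcomes". Quantitative data analysis gives the method: "Bias corrected bootstrap confidence intervals will be used to test moderators and mediators", with 10,000 resamples, a regression-based approach and the PROCESS macro. The same section presents the study as designed to assess the theorised model of maintenance and change.

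Table 1 gives the timing. The rows "Depression Anxiety Stress Scale" and "Work and Social Adjustment Scale" are marked at baseline, end of 6 weeks and 6 months. The rows "The Autonomous and Controlled Motivations for Treatment Questionnaire" and "Visual analogue scale: confidence and motivation to change", and those for cognitive flexibility and therapist alliance, are marked at baseline and end of 6 weeks only.

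**The concern.** A mediation claim says that treatment changed the mediator and that this change then altered the outcome. Randomisation protects the path from arm to mediator and the path from arm to BMI. It does not protect the path from mediator to BMI. If mediator and BMI are first measured after baseline at the same point, the data carry no order. Better mood leading to weight gain, weight gain leading to better mood, and a common cause of both all produce a non-zero indirect effect.

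Evaluating mediators is part of the second study aim. A positive mediation result at week 6 would be read as support for the cognitive-interpersonal model, yet as scheduled it could equally arise with the causal direction reversed.

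**Working it through.** **Step 1: timing, from Table 1 and Patient assessments.**

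| Measure | Between baseline and week 6 | End of week 6 | 6 months |
|---|---|---|---|
| DASS-21, Work and Social Adjustment Scale | none | yes | yes |
| ACMTQ, visual analogue scales, cognitive flexibility, therapist alliance | none | yes | none |
| Peer-mentor alliance | weekly, intervention arm only | – | – |
| BMI | weekly | yes (primary) | yes |
| EDE-Q | none | yes (secondary) | yes |
| Daily survey (mood, motivation, hope, compliance, connection) | daily | – | – |

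Six of the seven named mediators have no post-baseline value before the week-6 outcome. The seventh is undefined in the control arm, so it cannot mediate the between-arm contrast. For 6-month BMI and EDE-Q, the week-6 questionnaires do come first.

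**Step 2: why the product term is non-zero without mediation.** Let T be the arm (0/1), Y week-6 BMI in SD units and M the mediator, with no effect of M on Y. The planned test estimates a (T to M) and b (M to Y given T), and tests a × b.

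- Reverse causation: Y = dT + e and M = rY + √(1 − r²)·u. Then a = rd and b = r, so a × b = r²d. With d = 0.33 and r = 0.5 this is 0.25 × 0.33 = 0.083, so a quarter of the BMI effect appears mediated.
- Shared cause: T shifts M by δ, and the residuals of M and Y correlate at r. Then a × b = δr. With δ = 0.33 and r = 0.3 this is 0.099.

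**Step 3: the plan's own figures.** The protocol states no error rate for the mediation test. Its effect sizes, under Sample size, are 0.29 (prior research) and 0.33 (detectable with 75 per arm). The 0.33 reproduces for a two-sided paired t test: (1.960 + 0.842)/√75 = 0.324, and 0.328 by the exact noncentral t. For a two-sample comparison of 75 per arm the detectable effect is 2.802 × √(2/75) = 0.458, or 0.46 exactly. Using 0.29 and 0.33 as between-arm differences is therefore an assumption; 0.46 is shown alongside.

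**Step 4: simulation.** 75 per arm, bias-corrected bootstrap 95% interval, 2,000 resamples in place of 10,000, 300 to 1,000 trials per setting (Monte Carlo standard error at most √(0.25/300) = 2.9 percentage points). The mediator never affects BMI. All values of r, and all arm effects on the mediator, are assumptions.

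| Setting | Mediation declared, per mediator |
|---|---|
| Treatment changes nothing, r 0.3–0.5 | 6–7% |
| Reverse causation, d = 0.29, r 0.2–0.7 | 9–26% |
| Reverse causation, d = 0.33, r 0.2–0.7 | 8–31% |
| Reverse causation, d = 0.46, r 0.2–0.7 | 10–54% |
| Shared cause, arm shifts mediator 0.20 SD, r 0.2–0.5 | 24–29% |
| Shared cause, 0.33 SD, r 0.2–0.5 | 45–58% |
| Shared cause, 0.46 SD, r 0.2–0.5 | 66–81% |

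With six mediators under reverse causation (r 0.3–0.5), at least one is declared in 38–54% of trials at d = 0.33. Six independent 5% tests alone would give 1 − 0.95⁶ = 26%. Adding baseline BMI and the baseline mediator as covariates still left 7–40% under reverse causation.

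**Step 5: does ordering help?** Reverse causation only, d 0.33–0.8, r 0.3–0.5, mediator at week 3 and BMI at week 6:

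| Analysis | Mediation declared |
|---|---|
| Same-visit mediator | 14–72% |
| Week-3 mediator, unadjusted | 10–44% |
| Week-3 mediator, adjusted for week-3 BMI in both equations | 0.3–1.5% |

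Earlier timing alone is not enough; adjustment for weight at the same time does most of the work.

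**The case against.** **The pairing of time points is not spelled out.** The article names the method but no lags or covariates, and a condensed article commonly leaves these to the analysis plan. That is fair as to detail. However, the mediators, the outcome they are assigned to and the schedule are all stated, and no analysis plan can create a mid-treatment value for questionnaires not given then.

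**Ordered data already exist.** Hope is among the tertiary domains, and the only hope measure described is the daily survey. Daily and weekly trajectories are planned as predictors of outcome, and week-6 questionnaires precede the 6-month outcomes. This stands and limits the point to week-6 outcomes. But Outcome assessment gives the daily items a separate predictive role rather than placing them among the mediators.

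**A shared cause troubles mediation in any trial.** This also stands. When the week-3 analysis adjusted for week-3 weight was applied to a persistent shared cause, false mediation remained at 7–38% for an arm effect of 0.5 SD on the mediator and 4–17% for 0.3 SD, depending on the assumed autocorrelation of weight.

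**Mediation is a tertiary question in an exploratory, feasibility-scale study.** True, and it limits the weight of the point. But being exploratory excuses imprecision, not a test that answers alike for opposite causal directions.

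**Stronger readings.** A reader might infer that the trial will usually declare mediation where there is none. The documents do not support that: they give no arm effect on any mediator and no mediator–BMI correlation, and the rate is near nominal if treatment changes nothing. A reader might also object that moderators are not tied to baseline values; that is detail an article may leave out, and is no finding.

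**Conclusion.** The point holds for mediation of week-6 BMI and week-6 EDE-Q by the named questionnaires. It rests on the protocol's own schedule and mediator list. Its size is conditional: about 8 to 31% false mediation per mediator under pure reverse causation at 0.29 to 0.33, and about 45 to 81% where the arm shifts the mediator by 0.33 to 0.46 SD and a shared cause links it to BMI. These rates depend on assumed correlations (0.2–0.7 and 0.2–0.5 respectively) and on reading the protocol's effect sizes as between-arm differences. The shared-cause figures are not purely a timing defect.

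The primary arm comparison is unaffected, and the 6-month outcomes do not share this problem. A change is worth making because it is cheap and bears on a stated aim.

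**What to change.** Amend Outcome assessment and Quantitative data analysis as follows.

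- (a) Use the week-6 questionnaires as mediators of 6-month BMI and EDE-Q only, adjusting for the baseline mediator and for the baseline and week-6 values of the outcome.
- (b) For week-6 BMI, use early daily-survey items (mood, motivation, hope, connection), for example averaged over weeks 1 to 3, with adjustment for clinician-recorded weight at the same time. Both are already collected, and the control arm follows the same assessment schedule. The window is a choice to be fixed in advance.
- (c) Report any same-visit week-6 analysis, including that of EDE-Q, as an association.

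No new data are needed, but there are costs. Cognitive flexibility, therapist alliance and work and social adjustment have no daily item, so they are no longer claimed as mediators at week 6, although thinking style and interpersonal relationships are two of the model's four maintaining factors. Adjusting for concurrent weight may absorb part of a true early effect. Option (a) relies on 6-month BMI, which is self-reported. Re-timing does not remove bias from an unmeasured shared cause, and the report should say so.

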## Expected results

### Quantitative data analysis

This exploratory hypothesis testing study is designed to assess our theorized model of maintenance and change in anorexia nervosa (Figure 1). The time trend in weight and symptoms of anorexia nervosa over 6 months for each person will be estimated using mixed-effects regression models with structured covariance patterns to account for autocorrelation of repeated measures [51,52]. Models will test for linear and curvilinear change over time. The difference between the groups in the rate of change over time will then be examined using group-by-time interaction. Variation within individuals will be modelled as ‘Level 1’ and will include daily survey data, and variation between individuals (including the intercept and slope) will be modelled as ‘Level 2’. All continuous variables will be grand mean centred and results will be modelled using random intercept and slopes. Separate analyses will regress (1) participants’ weight change (baseline to 6-month follow-up) on mood, (2) participants’ weight change (baseline to 6-month follow-up) on motivation to change and on confidence to change and (3) treatment condition on repeated assessment of weight.

Moderator and mediator analyses will be performed using the regression-based bootstrapping approach described by Hayes [53]. Bias corrected bootstrap confidence intervals will be used to test moderators and mediators based upon 10,000 bootstrap samples. Analyses will be conducted using the PROCESS macro [54].

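### Three EDE-Q readings barely support the person-level growth model planned for symptoms, and its slope test does not directly give the 6-week and 6-month arm differences named as outcomes

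*Protocol article*

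**What the plan says.** The Quantitative data analysis section describes a single approach for both outcomes: "The time trend in weight and symptoms of anorexia nervosa over 6 months for each person will be estimated using mixed-effects regression models". The covariance side is given as "mixed-effects regression models with structured covariance patterns to account for autocorrelation of repeated measures", with no structure named. On the shape of the trend it says "Models will test for linear and curvilinear change over time". The arms are then compared on rate of change, through a group-by-time interaction.

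On the random effects, two nearby sentences differ. One has a single slope: "variation between individuals (including the intercept and slope) will be modelled as" the second level. The other has the plural: "results will be modelled using random intercept and slopes". Neither says whether the curvilinear term is random.

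The Outcome assessment section defines the secondary symptom outcome as "eating disorder symptoms (assessed by EDE-Q scores) at 6-week and 6-month follow-up", compared between arms. Table 1 marks the EDE-Q at baseline, end of 6 weeks and 6-month follow-up only. The weekly symptom measure is a different 12-item instrument, limited to the 6 weeks, and has another role: "the trajectories of change in eating disorder symptoms (weekly EDE-QS") are to predict outcomes. Table 1 has BMI at baseline, weekly for 6 weeks and at 6 months.

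**The concern.** The model fits the BMI schedule but not the EDE-Q schedule. A person-level curve with intercept, linear and quadratic terms passes exactly through three points, leaving nothing from which to separate residual error. The weekly short form cannot fill the gap, because it is another scale and stops at week 6.

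The estimand is a second mismatch. The outcome section asks for the arm difference at two named visits, whereas the analysis section tests a difference in slope. A slope summarises both visits in one number and, if linear, fixes the ratio between them. That matters for a 6-week intervention, whose effect could appear by week 6 and then level off or fade.

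At stake are a clean fit for a stated secondary outcome, variance components that can be interpreted, and a direct answer at each of the two visits.

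**Working it through.** **1. What three readings can identify.** Inputs: EDE-Q at 0, 6 and 26 weeks (Table 1, taking 6 months from baseline as 26 weeks). A 3x3 covariance matrix has 3 x 4 / 2 = 6 distinct elements. The model covariance is V = ZGZ' + R, where G is the unstructured random-effects covariance and R the residual covariance. Identification was checked by the rank of the derivative of the distinct elements of V with respect to the parameters.

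| Random effects | Residual | Parameters | Rank | Identified |
|---|---|---|---|---|
| Intercept, linear | independent | 3 + 1 = 4 | 4 | yes |
| Intercept, linear | AR(1) | 3 + 2 = 5 | 5 | yes |
| Intercept, linear | Toeplitz | 3 + 3 = 6 | 5 | no |
| Intercept, linear | heterogeneous AR(1) | 3 + 4 = 7 | 6 | no |
| Intercept, linear, quadratic | independent | 6 + 1 = 7 | 6 | no |
| Intercept, linear, quadratic | AR(1) | 6 + 2 = 8 | 6 | no |

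Sample size does not change these ranks. BMI has 8 occasions, hence 8 x 9 / 2 = 36 elements, and every variant above is identified.

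**2. How weak the 5-parameter version is.** Assumed values, not from the protocol: intercept variance 1.0, covariance -0.05, slope variance 0.08 per month squared, residual variance 0.4, AR(1) correlation 0.3, N = 150 with complete data. The expected standard error of the autocorrelation is about 0.47, larger than the parameter itself. The standard error of the residual variance rises from about 0.05 with independent residuals to about 0.31. Another assumed set of variances gave about 0.24 and 0.16, so the sizes depend on the assumptions; the direction does not.

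**3. Does this damage the arm comparison?** Assumed true correlations: 0.80 (0 to 6 weeks), 0.65 (6 weeks to 6 months), 0.50 (0 to 6 months), with equal variances. Each covariance model was fitted to that matrix, with the means left free, and the model standard error of change was divided by the true one.

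| Model fitted | 6 weeks | 6 months |
|---|---|---|
| Intercept, linear slope, independent residuals | 0.985 | 0.992 |
| Intercept, linear slope, AR(1) by visit order | 1.016 | 1.013 |
| Intercept, linear and quadratic slopes, independent residuals | 1.00 | 1.00 |
| Intercept only | 1.32 | 0.84 |

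In the first two rows a nominal 5% test has a true size between 4.6% and 5.3%. In the third row the split between G and R is undetermined, but V itself is recovered exactly. The last row uses the average correlation (0.80 + 0.65 + 0.50)/3 = 0.65, so the SD of change is sqrt(2 x 0.35) = 0.837, against a true sqrt(2 x 0.20) = 0.632 and sqrt(2 x 0.50) = 1.000.

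**4. Slope against visit differences.** With a linear trend and arm-specific slopes differing by d per week, the arm difference in change is 6d at week 6 and 26d at week 26. The ratio is 6/26 = 0.23 whatever the data show. If follow-up were instead counted from the end of the intervention, it would be 6/32 = 0.19.

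**The case against.** The strongest reply is that the over-parameterised model is not clearly the one planned. The curvilinear term is nowhere called random, and the Level 2 sentence has a single slope. A fixed quadratic adds no covariance parameters, and random intercept plus linear slope plus AR(1) is identified. This stands: a reader might infer that the EDE-Q model cannot be estimated, and the text does not support that on every reading.

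A reader might also infer badly wrong standard errors, 16% too small at 6 months and 32% too large at 6 weeks. Those figures belong only to a random-intercept-only fallback under one assumed set of correlations. The protocol states no such fallback; it specifies slopes and autocorrelation. With the slope kept, the errors are under 2%. That an analyst would improvise after a failed fit is likewise an inference, since an analysis plan not shown may fix the structure. Nor does the article say that autocorrelation is indexed by visit order.

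Finally, a quadratic term interacting with arm would free the means at the three visits, so the two differences could be derived from the coefficients. That is true, but the stated comparison is a difference in rate of change, and the two visit contrasts would still have to be extracted from it.

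What remains is a mismatch between the model stated for symptoms and the schedule and contrasts stated for the EDE-Q.

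**Conclusion.** The point holds in limited form. With three EDE-Q readings, the fullest reading of the planned model is not identified (7 or 8 covariance parameters against 6). The leanest reading that keeps both a random slope and AR(1) is identified (5 of 6), but its components are poorly separated. The consequence is mainly convergence trouble and variance components that should not be interpreted; it is not a distorted arm comparison, as long as the random slope is kept. The counts and ranks rest only on the schedule; the standard-error ratios rest on the assumed correlations.

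The more practical weakness is that a rate-of-change test does not directly report the two EDE-Q differences named as secondary outcomes, and a linear version ties the 6-week difference to about 23% of the 6-month one, counting 6 months from baseline. The change is worth making because it is cheap. It concerns a secondary outcome in an exploratory study and does not touch the identifiability of the BMI model.

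**What to change.** For the EDE-Q, replace the growth model with a repeated-measures model that has visit as a category (baseline, 6 weeks, 6 months), arm by visit, and an unstructured 3x3 covariance, which uses 6 parameters for 6 elements. Report the arm difference at 6 weeks and at 6 months. Keep growth curves for the weekly BMI series, stating which slopes are random and defining any autocorrelation on the actual time between readings.

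The cost is about two sentences of analysis wording and no new data. The per-person EDE-Q trend is given up, but three readings barely support it.
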